### Interventions

#### Prehabilitation program

Patients in the prehabilitation group will participate in a three-week (three sessions per week, nine sessions in total) supervised physical exercise training program prior to colorectal resection. The prehabilitation program is based on the program developed by Dunne et al. [25, 28], which has been shown to be feasible in sedentary healthy volunteers [28], and later demonstrated to deliver improvements in CPET scores and perceived health-related quality of life prior to hepatic resection [25]. In the studies of Dunne et al. [25, 28] prehabilitation consisted of twelve interval training sessions over a four-week period, whereas in the present study patients will perform nine preoperative sessions of individually-tailored interval training (personalized prehabilitation) over a three-week period. In the literature, it has been shown that as little as six sessions of ‘all-out’ high-intensity interval training over two weeks is sufficient to enhance cardiorespiratory fitness and improve skeletal muscle oxidative capacity in untrained and recreationally active individuals [38, 39]. However, a comparison with our patients with colorectal cancer and a low cardiorespiratory fitness cannot be made, because their ‘all-out’ exercise program differs from our exercise intervention, as ‘all-out’ exercise may not be safe, tolerable, or appealing for our patient group.

Patients will prehabilitate on Monday, Wednesday, and Friday, or on Tuesday, Thursday, and Saturday to improve their physical fitness preoperatively. Each 60-minute training session consists of moderate-to-high intensity interval training to improve cardiorespiratory fitness, and resistance training to improve peripheral muscle strength (see Tables 1 and 2). The interval training program will be tailored to each individual patient, based on the results of the CPET. The training sessions will be supervised by a selected group of trained physical therapists in community physical therapy practices in de adherence area of the hospitals. Additionally, the patient performs unsupervised home exercises at a moderate exercise intensity (e.g., walking, cycling, or stair climbing) twice a week for at least 30 minute, as checked by the physical therapist. We added these functional exercises to the prehabilitation program as de Vreede et al. [40] demonstrated that functional-task exercises are effective at improving functional task performance in healthy elderly women. Hence, home-based functional exercises that are of relevance for a patient may have an important role in helping patients to mobilize quickly postoperatively, to be physically active throughout the hospitalization period postoperatively, and to maintain independent physical functioning. Indeed, prehabilitation ideally should not focus merely on the preoperative period. Postoperatively, hospital culture and infrastructure should stimulate the patient to be physically active. However, in most hospitals health care is entirely organized around the patient’s bed [41], which invites patients to lie in bed, even without a medical reason. Bed-centered care probably also hampers the effectiveness of prehabilitation to improve postoperative outcomes.

**Table 1 Tab1:** Content of the three-week interval training program

	Duration	Intensity^a^
Warm-up	7 min	50%
Interval session	30 min	Work interval: 120% Recovery interval: 50%
Week 1, session 1, 2, and 3	Work interval: 120 s Recovery interval: 180 s	
Week 2, session 4, 5, and 6	Work interval: 140 s Recovery interval: 160 s	
Week 3, session 7, 8, and 9	Work interval: 160 s Recovery interval 140 s	
Cool-down	3 min	60%

^a^: Expressed as a percentage of the individually achieved work rate (in Watt) at the ventilatory anaerobic threshold obtained from the cardiopulmonary exercise test

**Table 2 Tab2:** Content of the three-week peripheral resistance training program^a^

	Repetitions^b^	Duration	Intensity^c^
Week 1, session 1, 2, and 3	3 × 8 repetitions	20 min	70% of 1RM
Week 2, session 4, 5, and 6	3 × 8 repetitions	20 min	76% of 1RM
Week 3, session 7, 8, and 9	3 × 8 repetitions	20 min	82% of 1RM

^a^: Peripheral resistance training of the large muscle groups of the lower and upper extremities using open and closed kinetic chain exercises (without physical therapy equipment or machines): crouching by means of squat exercises (primary muscle group: quadriceps femoris; secondary muscle groups: gluteal muscles, hamstring muscles, and gastrocnemius muscle), pulling by means of pulley exercises (primary muscle groups: latissimus dorsi muscle and rhomboid muscles; secondary muscle groups: biceps brachii muscle, rotator cuff, and trapezius muscle), pushing by means of pulley exercises (primary muscle group: pectoral muscles; secondary muscle groups: shoulder muscles, triceps brachii muscle), and lifting by means of pulley exercises (primary muscle groups: trunk muscles and shoulder muscles; secondary muscle groups: quadriceps femoris, gluteal muscles, and trapezius muscle)

^b^: Rest intervals of 60-90 s between each set of repetitions

^c^: Based on the 10RM, the patient’s 1RM was determined using the Oddvar Holten diagram

Abbreviations: 1RM, one-repetition maximum; 10RM, ten-repetition maximum

Patients with colon cancer or dysplasia will participate in the prehabilitation program in the time between contemplation of surgery and the procedure, whereas patients with rectal cancer, in case neoadjuvant therapy is needed, will complete the physical exercise training program *prior to* radiotherapy (in case of neoadjuvant radiotherapy, 5 × 5 Gy) or in the twelve-week period *after* neoadjuvant chemoradiotherapy (training in the last three weeks before surgery).

#### Usual care group

Patients in the control group receive usual care and will not participate in a prehabilitation program. In addition, no advice about physical exercise training is offered to them.

### Measurements

Both the prehabilitation group and usual care group will participate in a series of outcome measure assessments at baseline, seven days postoperatively, and 30 days postoperatively, whereas the prehabilitation group will participate in a series of outcome measure assessments after the three-week prehabilitation program as well (see Table 3).

**Table 3 Tab3:** Schedule of enrolment, interventions, and assessments

STUDY PERIOD	Enrolment	Allocation	Post-allocation					Follow-up	
			Pre-prehabilitation	Prehabilitation			Post-prehabilitation		
TIMEPOINT	-t_1_	0		Week 1	Week 2	Week 3		Day 7 post-surgery	Day 30 post-surgery
ENROLMENT:									
Eligibility screening	X								
VSAQ score (METs)	X								
Informed consent	X								
Allocation		X							
CPET	X								
INTERVENTIONS:									
Intervention group (prehabilitation program)									
Usual care group									
ASSESSMENTS:									
Baseline characteristics	X								
SNAQ score (0-5)	X								
VAT on CPET (mL/kg/min)			X				X^a^		
TUG test (s)			X				X^a^		
Muscle strength test			X				X^a^		
IADL			X						X
GDS 15			X						X
EORTC QLQ-C30			X						
GFI			X						X
Brief illness perception questionnaire			X				X^a^		
EQ-5D			X				X^a^		
Postoperative complications								X	X

^a^: Only for patients in the prehabilitation group

Abbreviations: CPET, cardiopulmonary exercise test; EORTC QLQ-C30, quality of life questionnaire of the European organisation for research and treatment of cancer; EQ-5D, EuroQol 5D; GDS 15, geriatric depression scale 15; GFI, Groningen frailty indicator; IADL, instrumental activities of daily living; MET, metabolic equivalent of task; SNAQ, short nutritional assessment questionnaire; TUG, timed up-and-go; VAT, ventilatory anaerobic threshold; VSAQ, veterans-specific activity questionnaire

#### Cardiopulmonary exercise test

A CPET will be used at baseline to assess cardiorespiratory fitness, as indicated by the VAT, in order to select and thereupon advice/invite eligible patients to participate in the study. For patients in the prehabilitation group, a second CPET will be used to investigate the effect of the prehabilitation program on cardiorespiratory fitness (single-arm study design). Patients free from any absolute and/or relative exclusion criteria, as stated by the American Thoracic Society and American College of Chest Physicians position statement [42], will be able to perform the CPET. The following standardized pre-test instructions will be given to the patients: 1) consume the last (light) meal at least 2 hours before exercise testing, 2) adhere to usual use of medication, and 3) wear comfortable sporting clothes and shoes. The CPET will be performed under controlled conditions at the lung function department of both hospitals, using a calibrated electronically braked cycle ergometer (Ergoline, Ergoselect 100, Bitz, Germany at Medisch Spectrum Twente and Lode Excalibur Sport, Lode BV, Groningen, the Netherlands at Ziekenhuisgroep Twente). Seat height will be adjusted to the patient’s leg length. During the CPET, patients breathe through a facemask (Hans Rudolph, Kansas City, MO, USA) connected to a Triple V volume transducer to perform breath-by-breath measurements of oxygen uptake, carbon dioxide production, respiratory flow, and volume parameters (Oxycon Pro, Jaeger, Hoechberg, Germany). In both hospitals the same respiratory gas analysis system will be used. Before each CPET at the Medisch Spectrum Twente and each morning at the Ziekenhuisgroep Twente, flow-volume calibration (three-liter syringe) and gas calibration (ambient air and a gas mixture of 16% oxygen and 5% carbon dioxide) will be performed, and ambient conditions are set. Twelve-lead electrocardiography will be used to continuously monitor heart rate during the test. Blood pressure (SunTech Tango+, SunTech Medical, Inc., Marrisville, NC, USA) will be automatically measured every three minutes to be aware of extreme hypertension or to detect hypotension. Oxygen saturation (Nonin 9600, Nonin Medical, Inc., Plymouth, MN, USA) is continuously recorded during the test by finger pulse oximetry.

After the test protocol is explained to the patient, the CPET starts with a two-minute rest period during which baseline cardiopulmonary data are collected. The patient then starts unloaded cycling at a pedaling frequency of 60-80 rotations per minute for three minutes, where after the work rate will be increased every minute by 5 to 15 W, depending on the patient’s physical fitness level and aimed at reaching a maximal effort within eight to twelve minutes [43]. The CPET continues until the patient is unable to maintain a pedaling frequency above 60 rotations per minute due to volitional exhaustion and despite strong verbal encouragement. The CPET will be considered to be at or near the maximal level when the patient shows clinical signs of intense effort (e.g., unsteady biking, sweating, and clear unwillingness to continue exercising despite strong encouragement), when the patient is unable to maintain a pedaling frequency above 60 rotations per minute, and when at least one of the following criteria is met: a heart rate at peak exercise of > 95% of predicted (predicted peak heart rate [beats/min] = 208 – 0.7 × age [years]) or a respiratory exchange ratio at peak exercise of > 1.10. After termination of the CPET, the patient will complete a recovery phase of unloaded cycling at a low pedaling frequency for five minutes. A clear description of adverse events and early test termination will be given.

During the CPET, absolute values at peak exercise are calculated as the average value over the last 30 seconds prior to termination of the test. Peak heart rate is defined as the highest heart rate achieved during the CPET. Cardiorespiratory fitness will be assessed by determining the VAT, by evaluating the peak oxygen uptake in case the patient performed a maximal effort, and by calculating the oxygen uptake efficiency slope [44]. The VAT will be detected by using the V-slope method, which is based on analyzing the slopes of oxygen uptake and carbon dioxide production. The VAT can be determined by using computerized regression analysis of these slopes. The point at which the linear slope of the relation between the carbon dioxide production and oxygen uptake changes, is called the VAT [45]. When the V-slope is expected to be unreliable, the ventilatory equivalents will be used to determine the VAT [46]. In this ventilatory equivalents method, the VAT will be defined as the point at which the ventilatory equivalent for oxygen and the partial end-tidal oxygen tension reached a minimum and thereafter began to rise in a consistent manner, coinciding with an unchanged ventilatory equivalent for carbon dioxide and partial end-tidal carbon dioxide tension [42]. The inter-observer variability in a preoperatively measured VAT has been reported to be acceptable for experienced clinicians [7], and DeCato et al. [47] recently reported short-term repeatability for CPET parameters in healthy participants in a similar test protocol, and they found no evidence for a learning effect and no significant differences in variability related to sex, age, fitness level, and diurnal factors.

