The literature shows that high-risk patients (those patients with a higher likelihood of postoperative complications), who participated in a physical exercise training program prior to elective surgery (prehabilitation), improved their cardiorespiratory fitness [23–25], which has led to the hypothesis that postoperative complications can be reduced by prehabilitation [23, 25–27]. Dunne et al. [28] designed a four-week high-intensity interval training program based on the work rate at the VAT for patients prior to hepatic resection. Their aim was to assess feasibility and to improve the preoperative VAT by 1.5 mL/kg/min (a 10% increase). They found their program to be feasible in sedentary healthy volunteers, resulting in a > 10% improvement in cardiorespiratory fitness (VAT). Using preoperative risk stratification, a 10% improvement in cardiorespiratory fitness in patients undergoing hepatic resection would shift 30% of the high-risk patient group to a low-risk patient group [28].

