The primary objective of this randomized controlled trial is to evaluate the hypothesis that a three-week prehabilitation program (intervention group) will reduce the number of postoperative complications from 50% to 20% in patients with a preoperative VAT < 11 mL/kg/min who will undergo elective colorectal resection for colorectal cancer or dysplasia grade I, II, or III, when compared to usual care (control group).

The secondary objectives are 1) to observe whether changes in preoperative cardiorespiratory fitness occur in the intervention group (prehabilitation, single-arm study design), 2) to evaluate the effect of the prehabilitation program on length of stay, 3) to examine whether patients with a preoperative VAT ≥ 11 mL/kg/min, and who will therefore not be included in the randomized controlled trial, have fewer postoperative complications than patients in the prehabilitation or usual care group (for the prehabilitation group, we will use the post-prehabilitation CPET data), 4) to investigate the value of a limited geriatric assessment in this patient group to perform preoperative risk stratification, and 5) to evaluate the cost-effectiveness of prehabilitation in high-risk patients by performing a cost-effectiveness analysis.

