### Participants

To be eligible to participate in this study, a patient must meet all of the following inclusion criteria: 1) ≥ 60 years, 2) colorectal cancer or premalignant colorectal lesions (dysplasia grade I, II, or III) requiring colorectal resection, 3) undergoing elective colorectal resection at Medisch Spectrum Twente, Enschede, or at Ziekenhuisgroep Twente, Almelo, 4) having a life expectancy of more than 6 months as estimated by the surgeon, 5) has given informed consent to participate in this study, 6) a metabolic equivalents of task (MET) score ≤ 7 on the veterans-specific activity questionnaire (VSAQ), 7) able to perform a CPET, 8) a VAT < 11 mL/kg/min as measured at the baseline CPET, and 9) willing to perform prehabilitation at a community physical therapy practice in the adherence area of both hospitals. All patients not meeting these criteria will not be considered for inclusion. Participants can leave the study at any time for any reason if they wish to do so, without any consequences. The investigator can decide to withdraw a participant from the study for urgent medical reasons.

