#### Statistical analysis

Nominal variables will be presented as numbers with percentages. Continuous variables will be presented as mean ± SD, or as median and interquartile range, as appropriate. Data will be presented in tables and figures. All tests will be performed on the intention to treat population, and on the per-protocol population. Data distribution will be checked with help of an epidemiologist.

For categorical variables, chi-squared tests or Fisher’s Exact tests, as appropriate, will be performed to analyze the difference between the intervention and control group. For continuous variables this will be done by independent samples t-tests or Mann-Whitney U tests, as appropriate. A repeated measurements analysis (mixed models in SPSS) will be performed to assess changes over time in continuous variables. A cost-effectiveness analysis will be performed, with the use of quality adjusted life years. Withdrawn patients will be followed by checking the patient’s data file. We will use the intention-to-treat analysis to avoid various misleading artifacts.

When half of the patients needed that are calculated (43 patients) are included, a blinded independent data analyst will perform an interim analysis with a stopping rule according to O’Brien-Fleming [81]. If this interim analysis shows a significant difference in postoperative complications between the prehabilitation group and the usual care group (at *P* < 0.0054), this data analyst will contact the Medical Ethics Committee, and debate the outcome of the interim analysis and its eventual repercussions. Thereupon this committee will advise the principle investigator of the research team (JK) to decide to stop the inclusion in case of superiority. If the interim analysis shows no or minimal difference (< 10% on overall complications), the study will be stopped due to futility. Because of the interim analysis, the final *P*-value that is considered to be significant is reduced to *P* < 0.0492.

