The present study, like all studies do, bares some limitations. Firstly, merely patients in the prehabilitation group will perform a second CPET to investigate the effect of the prehabilitation program on cardiorespiratory fitness. Consequently, we are not able to investigate the changes in cardiorespiratory fitness in the preoperative waiting period in the usual care group. However, the waiting period in patients in the usual care group was kept as short as possible to prevent these patients to improve their level of fitness by organizing their own preoperative exercise training program. Moreover, a study in patients planned for elective hepatic resection for colorectal liver metastases reported no significant differences in CPET variables in the control group after a four-week waiting period [25]. Secondly, the prehabilitation program in the present study consists only of a preoperative exercise training program, while it was recently indicated that studies evaluating a prehabilitation program combined with a nutritional intervention before elective major surgery in adults are producing encouraging early results [31]. However, definitive clinical evidence of physical and nutritional prehabilitation is currently very limited [31, 85, 86]. Thirdly, up till now, patient inclusion appears to be challenging. Not all patients are able and/or willing to attend the prehabilitation program due to personal, logistical, and time limitations (e.g., restricted time availability between the first outpatient visit and surgery, living too far away from the community physical therapy practice, and/or no traveling opportunities, planned vacation prior to surgery, not interested in participation). Moreover, at the start of the present study patients in both groups were informed about the possible effects of prehabilitation. We experienced that some patients in the usual care group initiated preoperative physical exercise training themselves, possibly resulting in the risk that we will not be able to detect a difference between the prehabilitation and usual care group. Therefore, we made an amendment to the study protocol (approved in April 2016 by the Medical Ethics Committee Twente) in which patients in the prehabilitation group and the usual care group will be informed differently. The patients in the usual care group will not receive information about the possible effects of prehabilitation and their elective colorectal resection was planned at the earliest convenience. Fourthly, in the present study a geriatric assessment will be completed at baseline only. Baseline data as predictors of postoperative outcome may be confounded by the effect of the prehabilitation program. Therefore, only data from patients in the usual care group will be used to investigate the value of a limited geriatric assessment to perform preoperative risk stratification. However, the power for this secondary objective might be inadequate, as the sample size calculation was not based on this objective.

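### The CPET that selects patients on VAT < 11 is also the baseline for the uncontrolled VAT change, so part of any observed rise will be regression to the mean

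*Protocol article*

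**What the plan says.** The inclusion criteria (Participants) require "a VAT < 11 mL/kg/min as measured at the baseline CPET". The section on the cardiopulmonary exercise test gives that test two jobs: "A CPET will be used at baseline to assess cardiorespiratory fitness, as indicated by the VAT, in order to select" patients for the trial. The same section calls the post-training test the second CPET, so no separate qualifying test precedes the baseline. Table 3 lists a CPET at enrolment and a VAT before prehabilitation, but read with that section these are one test. Table 3 marks the post-training VAT as measured in the prehabilitation group only.

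The protocol describes the resulting difference in two ways. The first secondary objective is worded neutrally: "to observe whether changes in preoperative cardiorespiratory fitness occur in the intervention group (prehabilitation, single-arm study design"). The section on the exercise test is causal: "a second CPET will be used to investigate the effect of the prehabilitation program on cardiorespiratory fitness (single-arm study design"). For the analysis, the Statistical analysis section says: "A repeated measurements analysis (mixed models in SPSS) will be performed to assess changes over time in continuous variables".

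The first limitation in the Discussion concedes that "we are not able to investigate the changes in cardiorespiratory fitness in the preoperative waiting period in the usual care group". It then offers reassurance from a hepatic-resection study that "reported no significant differences in CPET variables in the control group after a four-week waiting period".

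**The concern.** A VAT reading is the patient's usual level plus day-to-day and measurement error. Keeping only readings below 11 retains patients whose error happened to be negative and drops some whose error happened to be positive. The error on the second test has no such selection, so the group mean is expected to rise with no change in fitness. A before-after comparison in one arm cannot separate this rise from a training effect, and a mixed model fitted to the selected patients alone does not remove it.

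The limitation in the Discussion concerns something else, namely true change in fitness during the wait. The unchanged hepatic-resection controls are not described as having been selected on a VAT cut-off, and controls not so selected would not show this artefact. The statements on repeatability and the absence of a learning effect (Background; Cardiopulmonary exercise test) limit the size of the shift but do not abolish it.

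At stake is the first-listed secondary objective. It is the trial's own evidence on whether the programme raises fitness, which is the mechanism behind the primary hypothesis. A small training effect could look larger than it is.

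**Working it through.** **Plan's own figure.** The protocol gives no expected VAT change, no mean or SD of VAT and no test-retest error, so there is nothing to reproduce for this outcome. The sample size of 39 per arm (50% versus 20%, alpha 0.0492, power 0.80) does reproduce, with power 0.803 at 39, and does not depend on the VAT change.

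**Inputs.** The cut-off of 11 mL/kg/min is from the protocol. The following are assumptions about first-test VAT in tested patients with VSAQ ≤ 7: normal distribution, mean μ 10.5 to 12, SD σ 2 to 3, and test-retest error SD s of 5 to 10% of 11 (0.55 to 1.10 mL/kg/min).

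**Formulas**, with true change set to zero:
- t = (11 − μ)/σ and λ = φ(t)/Φ(t)
- mean first reading of selected patients = μ − σλ
- 1 − ρ = (s/σ)², where ρ is reliability
- expected rise = (1 − ρ) × σ × λ

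**Middle case, μ = 11, σ = 2.5.** Here t = 0 and λ = 0.3989/0.5 = 0.798. The selected mean is 11 − 2.5 × 0.798 = 9.0.

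| Error (% of 11) | s | 1 − ρ | Expected rise (mL/kg/min) | % of 9.0 |
|---|---|---|---|---|
| 5 | 0.55 | 0.048 | 0.10 | 1.1 |
| 7.5 | 0.825 | 0.109 | 0.22 | 2.4 |
| 10 | 1.10 | 0.194 | 0.39 | 4.3 |

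**Ends of the grid.**
- Lowest (μ = 10.5, σ = 3, s = 0.55): λ = 0.695 and 1 − ρ = 0.0336. The rise is 0.0336 × 3 × 0.695 = 0.07, or 0.8% of a selected mean of 8.4.
- Highest (μ = 12, σ = 2, s = 1.10): λ = 1.141 and 1 − ρ = 0.3025. The rise is 0.3025 × 2 × 1.141 = 0.69, or 7.1% of a selected mean of 9.7.

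The benchmark in the Background is a 10% gain. No cell of this grid reaches it.

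**Outside the grid.** With mean 13, SD 3 and reliability 0.70, the rise is 1.14 mL/kg/min (12%). That needs an error SD of 3 × √0.30 = 1.64, about 15% of 11. The statement that the artefact is less than a 10% gain therefore depends on the assumed error range.

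**Effect on a test of change.** A paired t-test was simulated with 39 patients, no training effect and two-sided 0.05 (4,000 runs per setting), at (mean, SD) of (11, 2.5), (12, 2.5) and (12, 2). A significant increase appeared in 12 to 20% of runs at reliability 0.95, 19 to 36% at 0.90 and 35 to 64% at 0.80. The nominal rate in that direction is 2.5%.

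**The case against.** The objective as worded only observes whether fitness changes, and it is labelled single-arm. The secondary study parameter is simply VAT after the programme. The Discussion tells readers that usual-care patients are not retested. All this stands, and it narrows the textual fault mainly to the causal phrase in the section on the exercise test and to a limitation that leaves out the selection artefact.

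The size is entirely assumed. At 5% error the rise is only 0.07 to 0.17 mL/kg/min across the grid, and the top figure of 0.69 comes from one corner with reliability of about 0.70. The protocol's description of VAT as accurate and repeatable points away from that corner but does not settle the matter, because no error figure is given and the short-term repeatability cited comes from healthy participants.

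Three stronger readings are tempting and are not supported:
- **The whole VAT gain would be an artefact.** On the assumed grid, regression to the mean is part of a 10% gain and never all of it.
- **The share of patients moving from below to above 11 can be set against the Background's statement that "a 10% improvement in cardiorespiratory fitness in patients undergoing hepatic resection would shift 30% of the high-risk patient group to a low-risk patient group".** Crossing 11 is not a listed outcome, and that statement is a projection from hepatic resection, also used to justify the sample size. It is not a target for crossings in this trial.
- **The VAT change is the only support for the mechanism.** The protocol also cites earlier CPET improvement with the parent programme, and it retests muscle strength and functional mobility.

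**Conclusion.** The concern holds for the before-after VAT change. Its direction follows from the design for any imperfectly repeatable test: the expected change is biased upward. Its size is not determinable from the protocol. Under the stated assumptions it is about 0.07 to 0.7 mL/kg/min (1 to 7% of baseline), or 0.10 to 0.39 at mean 11 and SD 2.5. Attributing the whole change to the programme, as the section on the exercise test does, is therefore wrong.

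A reader might infer that the trial's main result is compromised. It is not. The primary outcome is a randomized comparison of complications between arms, and neither it nor the sample size uses the VAT change. This is a worthwhile correction to a secondary objective.

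**What to change.** 1. In the section on the exercise test, describe the before-after VAT difference as an observed, uncontrolled change, in line with the first secondary objective. Add regression to the mean from selection on the baseline reading to the first limitation in the Discussion.
2. Report the VAT change as observed and also net of the expected regression-to-the-mean shift. Estimate the shift from the first-test VATs of all tested patients with VSAQ ≤ 7, including those at 11 or above, whose baseline CPET is already done. Show the result over a stated range of test-retest error, because the trial does not measure that error.
3. Changes in oxygen uptake efficiency slope and peak oxygen uptake may be shown as supportive only. They come from the same selecting test and may also regress if their errors correlate with that of VAT. Peak uptake is evaluated only after a maximal effort.

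The cost is some rewording and a short calculation on data already held, with no new patients or tests. The drawback is that the net VAT gain will be smaller and will depend on an assumed error range.
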